## 8.6. OUTCOMES

### *8.6.1. Primary efficacy outcome*

All-cause deaths or all-cause re-admissions by 26 weeks from randomization (composite primary outcome).

### *8.6.2. Key secondary efficacy outcome*

8. Readmission due to severe malaria (defined as any treatment with parenteral quinine or artesunate, or presence of severe anaemia and treatment with oral antimalarials) by 26 weeks from randomization
9. Readmissions due to severe anaemia (defined as Hb <5g/dL or PCV <15% or requirement for blood transfusion based on other clinical indication) by 26 weeks from randomization
10. Readmission due to severe malarial anaemia (severe anaemia plus parenteral or oral antimalarial treatment) by 26 weeks from randomization

11. Readmission due to severe anaemia or severe malaria (composite outcome) by 26 weeks from randomization
12. All-cause mortality by 26 weeks from randomization
13. All-cause hospital readmission by 26 weeks from randomization
14. Clinic visits because of smear of RDT confirmed non-severe malaria by 26 weeks from randomization

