| Key Secondary efficacy outcomes | 1. Readmission due to severe malaria (defined as any treatment with parenteral quinine or artesunate, or presence of severe anaemia and treatment with oral antimalarials) by 26 weeks from randomization
2. Readmissions due to severe anaemia (defined as Hb <5g/dL or PCV <15% or requirement for blood transfusion based on other clinical indication) by 26 weeks from randomization
3. Readmission due to severe malarial anaemia (severe anaemia plus parenteral or oral antimalarial treatment) by 26 weeks from randomization
4. Readmission due to severe anaemia or severe malaria (composite outcome) by 26 weeks from randomization
5. All-cause mortality by 26 weeks from randomization
6. All-cause hospital readmission by 26 weeks from randomization
7. Clinic visits because of smear of RDT confirmed non-severe malaria                                                                                                                                                                                                                           |
| Safety outcomes                 | 1. Serious adverse events, excluding primary and secondary efficacy outcomes, by 26 weeks from randomization
2. Serious adverse events within 7 days after the start of each course of PMC, excluding primary and secondary efficacy outcomes.
3. Adverse events by 26 weeks from randomization
4. Adverse events within 7 days after start of each course of PMC.
5. QTc prolongation measured by electro cardio gram (ECG) 4-6 hours after 3rd dose of each course                                                                                                                                                                                                                                                                                                                                                                                                                                                                                                                                                                                                          |

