**Sites:** 7 hospitals, 4 in western Kenya and 3 in Uganda, in areas with moderate to intense malaria transmission. The number of hospitals will be expanded if recruitment if so required.

**Study Population:** Inclusion criteria: convalescent children aged less than 5 years and weighing  $\geq 5$  kg admitted with severe anaemia (haemoglobin  $< 5$ g/dL / Ht  $< 15\%$ ); clinically stable, able to take or switch to oral medication; post-transfusion Hb  $> 5$ g/dL. Exclusion criteria: blood loss due to trauma, malignancy, known bleeding disorders or sickle cell disease, known hypersensitivity to study drug, known heart conditions, non-resident in study area, previous participation in study, known need at enrolment for prohibited medication and scheduled surgery during the 6-month course of the study. HIV infection and cotrimoxazole prophylaxis are not exclusion criteria.

**Study Interventions:** Children in both arms will receive standard in-hospital care for severe anaemia (blood transfusion, often combined with quinine or artesunate IV/IM). All children will then receive a 3-day course of AL (whether they initially had malaria or not), which will be started in-hospital as soon as they are able to take oral medication, and will be completed at home after discharge. At 2 weeks after enrolment surviving children will be randomized to receive either a standard 3-day

courses of DP (Eurartesim®, Sigma Tau, Italy) or an identical placebo regimen at 2, 6 and 10 weeks after enrolment.

**Outcome Measures:** Primary: Death or all-cause re-admission by 6 months from randomization (composite primary outcome). Key secondary: 1) all-cause mortality, 2) all-cause hospital readmission, 3) readmissions due to severe anaemia or severe malaria (requiring parenteral quinine or artesunate), 4) non-severe all-cause sick-child clinic visits, 5) clinic visit because of RDT or microscopy confirmed non-severe malaria.

**Follow-up procedures:** Children will be followed for 6 months by passive case detection in 3 phases: Pre-PMC (2 weeks between discharge and randomisation); PMC (2-14 weeks post-discharge); post-PMC (extended follow period from 15 to 26 weeks post-discharge).

**Sample size:** A sample size of 520 children per arm (1040 total children) allows detection of a 25% reduction in the incidence rate from 1,152 per 1000 child years (530 per 1000 children per 24 weeks) to 864 per 1000 child years, with 10% loss to follow-up (power 80%,  $\alpha=0.05$ ).

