### *8.2.2. Why in this study population?*

The primary study population involves children with all-cause severe anaemia, rather than children with severe malarial anaemia, which was the study population in the previous trial in Malawi. The rationale for this is that subsequent observational analysis in Uganda and western Kenya of data of post-discharge follow-up showed that children admitted with severe anaemia appear to be at increased risk of readmission and death regardless of whether they have evidence of malaria infection at the time of admission. Second, the differentiation between severe anaemia and severe malarial anaemia is not always feasible as it is common practice in many hospitals in sub-Saharan Africa to start parenteral treatment with antimalarials before the laboratory diagnosis of malaria is available. Furthermore the interpretation of malaria diagnostic tests on admission may be complicated in children with a history of recent antimalarial treatment in the days just prior to admission.

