## 8.5. INTERVENTIONS

### *8.5.1. Standard in-hospital and post-discharge care (not study specific or study related)*

All care provided prior to and following enrolment of the patient in the study (at convalescence) will not be part of the study and will be per local (hospital) or national guideline with the exception of the full 3 day course of artemether-lumefantrine (AL) as described below. All details of non-study specific care provided by the hospital staff will be recorded in the study forms, including all drugs and dosages prescribed. The hospital teams providing care will be provided with updates of the latest national and local guidelines for in-hospital care.

*Blood transfusion and malaria treatment:* The standard in-hospital care for severe anaemia includes a blood transfusion (20mL/Kg whole blood or 10 mL/Kg Packed Red cells). In addition, patients suspected to have severe malarial anaemia also receive antimalarial treatment. In patients not able to take oral medication this consists of parenteral artesunate (2.4 mg/Kg at time 0, 12 and 24 hours), followed by a full 3 day course of artemether-lumefantrine (AL) once the patient is able to switch to oral medication. In some instances, when artesunate is not available, patients may receive parenteral quinine (10mg/kg every 8 hours) or i.m artemether. In those children who are able to take oral medication throughout, the 3-day course of AL is given without prior parenteral treatment with artesunate.

*Antibiotics* are commonly used during the in-hospital period and will be documented, but will not be part of the study intervention.

*Iron and folate supplementation* will not be part of the medication provided by the study until the time of randomisation at 2 weeks post-discharge. Until then, the use of haematinic supplementation is at the discretion of the treating clinicians. However, the hospital staff will be reminded that iron supplementation is not required during the first two weeks because the blood transfusion provided as part of the standard in-hospital care will contain adequate amounts of iron for the initial post-discharge period. See section 8.5.2.7, page 31 for details about iron supplementation during the PMC intervention period (i.e. from the first PMC dose at 2 weeks onwards).

*HIV testing*, see section 8.7.3.5, page 38.

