## **9.3. PROCEDURES FOR ASSESSING EFFICACY PARAMETERS**

### *9.3.1. Primary outcome*

*All-cause mortality* will be assessed during the visits at 2, 6, and 10 weeks to administer PMC and the end of study visit at 6 months.

*All-cause and disease specific re-admissions* will be assessed through passive case detection and through a questionnaire administered during the visits at 2, 6, 10 weeks and 6 months. Details of the admission and treatment provided will be recorded, where available, on special study forms including RDT or malaria smear results and use of antimalarials, to allow for differentiation between malaria, severe anaemia, and other syndromes.

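### The severe malaria readmission outcome leaves out i.m. artemether, and the malaria readmission outcomes have no test-confirmed version to show how far presumptive treatment dilutes them

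*Protocol*

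**What the plan says.** The numbering here follows protocol sections 8.6.2 and 8.6.3; section 3.1 lists the same key secondary outcomes as items 1 to 7.

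- **Outcome 8, severe malaria:** "Readmission due to severe malaria (defined as any treatment with parenteral quinine or artesunate, or presence of severe anaemia and treatment with oral antimalarials".
- **Outcome 10, severe malarial anaemia:** "Readmission due to severe malarial anaemia (severe anaemia plus parenteral or oral antimalarial treatment". No drug is named, so any parenteral antimalarial qualifies.
- **Outcome 11:** "Readmission due to severe anaemia or severe malaria (composite outcome". It inherits the definition of outcome 8.
- **Outcome 14, non-severe malaria clinic visits:** smear or RDT confirmation is required.
- **Outcome 15 (section 8.6.3, other secondary):** the outcome 10 criterion plus a parasite density above 5000 per microlitre.
- **Outcome 16 (section 8.6.3):** readmission for severe disease that is neither severe anaemia nor severe malaria.

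Three other sections bear on how these are scored. Section 8.2.2 says it is common for hospitals to "start parenteral treatment with antimalarials before the laboratory diagnosis of malaria is available". Section 8.5.1 says that when artesunate is unavailable, "patients may receive parenteral quinine (10mg/kg every 8 hours) or i.m artemether". Section 9.3.1 has readmission details recorded, where available, "including RDT or malaria smear results and use of antimalarials, to allow for differentiation between malaria, severe anaemia, and other syndromes".

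The summary in section 3.2 describes severe malaria by parenteral quinine or artesunate only and leaves out the oral limb of outcome 8.

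**The concern.** There are two faults, and both lie in definitions that the protocol itself fixes in sections 3.1 and 8.6.2.

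First, the drug list of outcome 8 is narrower than the care the protocol expects and narrower than that of outcome 10. Genuine malaria treated with i.m. artemether can be missed. If the child is not severely anaemic, the event moves to outcome 16, the natural check on whether any benefit is specific to malaria.

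Second, treatment stands in for diagnosis. Where treatment starts before the test result, a test-negative readmission can be scored as malaria. DP would not be expected to prevent such events, so they pull the rate ratio towards 1 and also leave outcome 16. Non-severe malaria needs a positive test and severe malaria does not.

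At stake are the size and interpretation of outcomes 8 and 10 and of part of outcome 11. Section 9.8 also expresses costs per case averted of severe anaemic malaria, so the case count may carry into the economic evaluation.

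**Working it through.** **1. Literal scoring of readmission types**

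| Readmission | Outcome 8 | Outcome 10 | Outcome 11 | Outcome 16 |
|---|---|---|---|---|
| Test-negative, no severe anaemia, parenteral artesunate or quinine | yes | no | yes | no |
| Test-negative, severe anaemia, oral antimalarial | yes | yes | yes | no |
| Malaria-positive, no severe anaemia (e.g. Hb 7 g/dL, no transfusion needed), i.m. artemether | **no** | no | **no** | **yes** |
| Severe anaemia, i.m. artemether, then oral AL | yes | yes | yes | no |
| Severe anaemia, i.m. artemether, no oral antimalarial | **no** | yes | yes | no |

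The third row is the event lost to outcome 16. The fifth is an internal contradiction: the readmission counts as severe malarial anaemia but not as severe malaria. In outcome 11 the drug definition matters only for children without severe anaemia, because severe anaemia qualifies by itself. For the same reason the missing oral limb in section 3.2 does not change who counts in that composite; it matters only if the summary wording is used for severe malaria alone.

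**2. Dilution**

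Let f be the share of control-arm events counted as malaria that are not malaria, and assume DP has no effect on them. Then RR_observed = (1 − f) × RR_true + f. The protocol gives neither f nor RR_true, so both are assumed.

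| RR_true | f = 10% | f = 20% | f = 40% |
|---|---|---|---|
| 0.30 | 0.37 | 0.44 | 0.58 |
| 0.50 | 0.55 | 0.60 | 0.70 |
| 0.70 | 0.73 | 0.76 | 0.82 |

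With RR_true = 0.50, for example, f = 20% gives 0.8 × 0.50 + 0.2 = 0.60. The apparent reduction falls from 50% to 40%, or to 30% at f = 40%.

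**3. What test confirmation would gain (illustration)**

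Section 8.8.1.1 gives 520 per arm with 10% loss, so 468 evaluable, and 530 control events per 1000 children over 24 weeks. Assume 30% of those events are scored as severe malaria. Control events = 468 × 0.53 × 0.30 = 74. Power = Φ(|ln RR| / √(1/E_c + 1/E_t) − 1.96), where E_c is control events and E_t = E_c × RR.

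Treatment-based definition, RR_true = 0.50:
- f = 20%: E_c = 74, RR = 0.60, power 77%.
- f = 40%: E_c = 74, RR = 0.70, power 51%.

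Perfect test confirmation, which keeps 74 × (1 − f) control events at RR = 0.50:
- f = 20%: E_c ≈ 60, power 87%.
- f = 40%: E_c ≈ 45, power 76%.

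Imperfect confirmation at f = 20%, if 25% to 30% of true malaria readmissions are untested or falsely negative: power 76% to 73%, no better than 77% without confirmation. At f = 10% with 20% of true cases lost, power is 83%, against 87% without confirmation.

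**The case against.** The strongest reply is that a treatment-based definition is a reasonable choice. Section 8.2.2 warns that recent antimalarials complicate admission tests, and section 9.3.1 records results only where available. This stands: step 3 shows that confirmation can cost as much power as it gains. It argues against replacing the definitions, but not against adding a confirmed version beside them.

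Outcome 15 already gives outcome 10 a parasitological companion. That also stands, but outcome 15 covers only anaemia, uses a high density threshold and sits among the other secondary outcomes. Outcome 8 has no test-confirmed counterpart.

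Table 1 lists parenteral artesunate or quinine for severe malaria, which matches outcome 8, and section 8.5.1 expects artemether only in some instances. The gap may therefore affect few events, but the sections still disagree.

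Four stronger readings are tempting and are not supported:

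- *Artemether-treated readmissions never count as malaria.* They count for outcome 10, and for outcome 8 when severe anaemia is present and oral AL follows.
- *Any severe-anaemia readmission will score as malaria because AL is universal.* The sentence "All children will then receive a 3-day course of AL (whether they initially had malaria or not" describes the enrolment course. For follow-up, section 8.5.7.1 ties antimalarials to a malaria diagnosis. AL after a test-negative readmission is possible, but the protocol does not make it routine.
- *Misclassification costs the whole fall from the 93% power that 74 true malaria events would give.* Those 74 include the non-malaria events, so even perfect testing reaches only 87% or 76%.
- *The pooled rate ratio of 0.22 in section 8.5.2.5 is the true effect.* It concerns any parasitaemia under monthly DP, whereas these outcomes run on through weeks 15 to 26 without drug.

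**Conclusion.** The point holds in a limited form. The drug list of outcome 8 disagrees with section 8.5.1 and with outcome 10, and literal scoring sends a malaria-positive, non-anaemic, artemether-treated readmission to outcome 16. Outcomes 8 and 10, and the non-anaemic malaria part of outcome 11, require no malaria test although the protocol says presumptive parenteral treatment is common.

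The likely result is dilution: with an assumed true rate ratio of 0.50, an observed 0.60 at f = 20% or 0.70 at f = 40%. This assumes that DP has no effect on the non-malaria events. The frequency of artemether use and the completeness of testing are also unknown.

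A reader might infer that the main result is threatened or that the definitions favour DP. Neither follows. The primary outcome is all-cause death or readmission and uses none of these definitions. Allocation is double-blind, so false malaria labels should arise similarly in both arms and mainly weaken the apparent effect.

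**What to change.** 1. In sections 3.1 and 8.6.2, change the parenteral limb of outcome 8 to any parenteral antimalarial, so that it agrees with outcome 10 and section 8.5.1.
2. Reconcile the summary in section 3.2, which also omits the oral limb.
3. Keep the treatment-based definitions of outcomes 8, 10 and 11 as the main ones.
4. Add a prespecified RDT- or smear-confirmed version of outcomes 8 and 10 and of the malaria part of outcome 11, from the results recorded under section 9.3.1. In that version, count treated but test-negative readmissions without severe anaemia under outcome 16.

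The cost is revised outcome wording, including the registration data of a trial already recruiting, and one extra table. The change should be dated before unblinding. No new data are needed and no clinical care changes. The drawback is that readmissions with no recorded test, or falsely negative after recent antimalarials, drop out of the confirmed version. Their number per arm should be shown beside it.

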#### *8.6.3. Other secondary efficacy outcomes*

15. Readmission due to severe malaria-specific anaemia (severe anaemia plus parenteral or oral antimalarial treatment and parasite density >5000/microlitre) by 26 weeks from randomization
16. Readmission due to severe disease other than severe anaemia and severe malaria by 26 weeks from randomization
17. Non-severe all-cause sick-child clinic visits by 26 weeks from randomization
18. Non-malaria sick child clinic visits by 26 weeks from randomization
19. Malaria infection at 6 month
20. Hb at 6 months
21. Any anaemia (Hb<11 g/dL), mild anaemia (Hb 8.0-10.99 g/dl) moderate anaemia (Hb 5.0-7.99 g/dL) and severe anaemia (Hb<5 g/dL) at 6 months
22. Weight-for-age, height-for-age, and height-for-weight Z-scores (standard deviation [SD] scores of reference population) at 6 months

#### *8.6.4. Tolerability and safety*

6. Serious adverse events, excluding primary and secondary efficacy outcomes, by 26 weeks from randomization
7. Serious adverse events within 7 days after the start of each course of PMC, excluding primary and secondary efficacy outcomes.
8. Adverse events by 26 weeks from randomization
9. Adverse events within 7 days after start of each course of PMC.
10. QTc prolongation measured by electro cardio gram (ECG) 4-6 hours after 3rd dose of each course

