#### *8.7.8.2. Verbal autopsy visit*

All parents of children who die will be visited at home as soon as possible for a detailed verbal autopsy interview using standardized questionnaires that will be used to categorize the potential cause of death as probable, possibly, or not malaria related.

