#### 9.6.2.3. Serious Adverse Event (SAE) or Serious Adverse Reaction (SAR)

Any adverse event or adverse reaction that results in death, is life-threatening\*, requires hospitalisation or prolongation of existing hospitalisation, results in persistent or significant disability or incapacity, or is a congenital anomaly or birth defect.

Comment: Medical judgement should be exercised in deciding whether an adverse event/reaction should be classified as serious in other situations. Important adverse events/reactions that are not immediately life-threatening or do not result in death or hospitalisation, but may jeopardise the subject or may require intervention to prevent one of the other outcomes listed in the definition above, should also be considered serious.

\*Life-threatening in the definition of a serious adverse event or serious adverse reaction refers to an event in which the subject was at risk of death at the time of the event. It does not refer to an event which hypothetically might have caused death if it were more severe.

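### Both SAE outcomes leave out every death and readmission, so no named outcome compares serious events by arm in the 7 days after each PMC course

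*Protocol*

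**What the plan says.** Section 8.6.4 names two outcomes for serious events, and Section 3.1 repeats both. The first is "Serious adverse events, excluding primary and secondary efficacy outcomes, by 26 weeks from randomization". The second is "Serious adverse events within 7 days after the start of each course of PMC, excluding primary and secondary efficacy outcomes".

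The excluded set is wide. The primary outcome in 8.6.1 is "All-cause deaths or all-cause re-admissions by 26 weeks from randomization (composite primary outcome". Section 8.6.2 adds "All-cause mortality by 26 weeks from randomization" and "All-cause hospital readmission by 26 weeks from randomization" as separate key secondary outcomes. Section 8.6.3 adds readmission for severe disease other than severe anaemia and severe malaria (item 16), "Non-severe all-cause sick-child clinic visits by 26 weeks from randomization" (item 17) and non-malaria sick-child visits (item 18).

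Section 9.6.2.3 defines an SAE by death, threat to life, an event that "requires hospitalisation or prolongation of existing hospitalisation", disability, or congenital anomaly. It also counts medically important events that lead to neither death nor admission. Section 9.6.1 says that confirmed grade 2-4 ECG abnormalities in the cardiac sub-study are reported as SAEs.

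Two further outcomes in 8.6.4 cover adverse events to 26 weeks (item 8) and within 7 days of each course (item 9). Neither carries an exclusion. Section 9.2.6 plans tabulation by arm and body system, without formal testing.

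**The concern.** Death and hospital admission are the two criteria that produce most SAEs in a trial of this kind, and both are efficacy outcomes here for any cause. Read literally, the exclusion therefore takes out a death or admission whether or not the study drug caused it.

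This matters most for the 7-day outcome, which exists to look for serious harm close to dosing. The primary objective in 7.2.1 asks whether PMC-DP is safe as well as superior. Section 11.8.1.2 names dose-dependent QTc prolongation as the main safety concern with piperaquine. Section 8.5.2.5 supports the safety of repeated DP with SAE risk against comparators, death counts by exposure, and the absence of sudden or unexplained deaths. This trial's own SAE outcomes, as defined, could not supply the same comparisons.

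**Working it through.** **Step 1. Subtract the excluded outcomes from the SAE definition.**

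| SAE criterion (9.6.2.3, 9.6.1) | Also an efficacy outcome? | Left in the SAE outcomes? |
|---|---|---|
| Death | Yes: primary and all-cause mortality | No |
| Hospitalisation | Yes: primary and all-cause readmission | No |
| Prolonged hospital stay | Arguably, as part of a readmission already counted | Unclear |
| Life-threatening, no admission or death | Not as such | Yes |
| Disability | Not as such | Yes |
| Medically important, no admission or death | Not as such | Yes |
| Confirmed grade 2-4 ECG abnormality | No | Yes, but ECGs are taken in 66 children only |

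The clinic-visit outcomes change little. Item 17 is limited to non-severe visits. Item 18 has no such limit, so a literal reading might remove some medically important events seen at a clinic; the conclusion does not depend on that.

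**Step 2. Look for a named outcome that compares serious events by arm within 7 days of a course.**

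- SAE outcome, 7 days: right window, but deaths and admissions are removed.
- AE outcome, 7 days (item 9): right window and no exclusion, but serious events are not separated from minor ones.
- Mortality, readmission and other-cause readmission (items 12, 13 and 16): right events, but counted to 26 weeks.
- Period split of the primary outcome (9.2.5.2, item 13): right events, but in blocks of weeks 2-14 and 15-26.

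None combines serious events with the 7-day window.

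**Step 3. Size of what is removed.** The protocol gives no expected SAE count, so there is no SAE figure to reproduce. The inputs come from 8.8.1.1: 520 per arm; 1.152 and 0.864 primary events per child-year; 0.530 and 0.398 events per child over 24 weeks; 10% loss to follow-up.

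Check of the stated 24-week rates: 1.152 × 24/52.18 = 0.530, as stated. 0.864 × 24/52.18 = 0.397, against the stated 0.398 (0.75 × 0.530 = 0.3975).

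- No loss: 520 × 0.530 = 275.6 placebo; 520 × 0.398 = 207.0 DP; total 482.6, about 483.
- 10% loss, 520 × 0.9 = 468 per arm: 468 × 0.530 = 248.0; 468 × 0.398 = 186.3; total 434.3, about 434.

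Each of these is a death or a readmission, so each meets the SAE definition and each is excluded.

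**Step 4. The 7-day windows.** Three courses give 3 × 7 = 21 days per child. Assume a constant rate, all three courses received and no loss.

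- Child-years per arm in the windows: 520 × 21/365.25 = 29.90.
- Placebo: 29.90 × 1.152 = 34.4 events.
- DP: 29.90 × 0.864 = 25.8 events.

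Cross-check: 21 of 168 days is 12.5%, and 12.5% of 275.6 and 207.0 is 34.5 and 25.9.

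These counts illustrate scale only. With 468 per arm they fall to 34.4 × 0.9 = 31.0 and 25.8 × 0.9 = 23.2. Section 4.1 says the risk is highest in the first 3 months after discharge, so a constant rate may understate the placebo count. The DP count could move either way, because protection is also expected to be strongest then.

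**The case against.** The strongest reply is that the trial still collects and compares these events.

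- Deaths and readmissions are compared by arm as primary and key secondary outcomes.
- A readmission for something other than malaria or anaemia has its own outcome (item 16), so it is not merged with the admissions that DP is meant to prevent.
- The primary outcome is also examined separately for weeks 2-14 and 15-26.
- Item 9 has no exclusion, so deaths and admissions within 7 days are eligible for it, and a split by seriousness could be added in the analysis plan.
- Individual SAE reporting with causality (9.6.3) and DMEC access to unblinded data (9.5.1) do not depend on how the two outcomes are worded.

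All of this stands, and it rules out several stronger readings that a reader might infer. One is that the SAE comparison is empty by construction. It is not: life-threatening, disabling and medically important events and confirmed ECG abnormalities remain. Another is that a drug-related death or admission would be visible only inside the composite. Items 12 and 16 contradict that. A third is that early harm can only be seen netted against benefit over 24 weeks, which overlooks the planned period split. Nor do the documents show that participants go unmonitored.

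The reply does not supply the missing comparison. The period split is 12 weeks wide, item 16 covers readmissions only and runs to 26 weeks, and item 9 mixes serious with minor events. A later analysis plan could add a table, but the exclusion is a rule this protocol states, not a detail it leaves open. Verbal autopsy does not fill the gap for deaths, since its stated purpose is to "categorize the potential cause of death as probable, possibly, or not malaria related".

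**Conclusion.** The point holds in this form. Both SAE outcomes lose every post-randomisation death and readmission and keep only a small residue, whose number the documents do not allow to be computed. As a result, the 7-day SAE outcome cannot do the job it was written for.

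About 434 to 483 events are removed from the overall SAE outcome, depending on whether the planned 10% loss is applied and provided the planning rates hold. About 34 placebo and 26 DP events would be removed from the 7-day outcome, under the constant-rate, full-course, no-loss assumptions above. They are removed from the SAE outcomes, not from the trial: all are analysed by arm as efficacy events. It is therefore a cheap improvement to the safety definitions and does not threaten the primary efficacy result.

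**What to change.** In 3.1 and 8.6.4, define both SAE outcomes as all SAEs by arm, including deaths and readmissions that also count for efficacy. Report them overall and within 7 days of the start of each course, by body system and cause. Keep the version that excludes efficacy events as a supplement. List by arm every death within 7 days of a course.

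The cost is a change of wording in two sections and a few extra tables. The SAE forms in 9.6.3 already record the nature, onset date, severity, outcome and causality of each event, so no new data are needed. The downside is that the same event appears in both efficacy and safety tables, which a footnote should state so that readers do not add the two.
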